#### **4.8. Inclusion and exclusion**

##### **4.8.1. Cluster level**

*Inclusion criteria*

- Secondary within Copper belt providence with grade 8 students

*Exclusion criteria*

- Schools involved in any other oral health intervention programs
- Boarding schools
- Single sex schools
- Special need schools

##### **4.8.2. Individual level**

Subjects will be recruited at their respective schools during baseline data collection.

*Inclusion criteria*

Adolescents studying in grade 8 at schools

### ***Exclusion criteria***

Adolescents with the following conditions will be excluded

- anodontia,
- severe dental fluorosis,
- Those who have received orthodontic treatment
- With special needs.

## **4.9. Data collection procedures**

### **4.9.1. Data collection tools and indices**

Data will be collected using self-administered structured questionnaire and oral clinical examination. The questionnaire (Appendix 1) will be in English and will inquire on; demographic information of the participant's oral health knowledge and related behaviors and impact of oral diseases on daily performance of the adolescent. It will further inquire on parental/guardian socio-economic status using international wealth index (Smits and Steendijk, 2015). The students will understand the questions for the reason that they are fluent in English language.

Oral clinical examination will be done in a well illuminated classroom by two trained and calibrated dentists. Examination will be done using dental explorer aided by a mouth mirror and artificial light. The participants' will be lying on a desk and the examiner seated behind the participant's head. Every examiner will have one recorder who will be seated close to the examiner to ensure that the findings are recorded correctly.

Data collection will be done in four phases; baseline, every six months after institution of intervention that is; first follow up (6 months), second follow up (12 months), third follow up (18 months) and last follow up (24 months). The data collected for every adolescent will be paired and analyzed in pair. The principal investigator will assign a range of numbers for each school to be used as adolescent's identity number for baseline and all follow ups. School teachers will then be requested to create a list of names according to attendance register of that school and assign numbers to the individual participants. A copy of list of names and ID numbers will be kept by head teacher in case the teacher responsible for health is absent. Data for each variable will be entered and analyzed as set (baseline, 1st, 2nd, 3rd and 4th follow up).

#### **4.9.2. Blinding**

Single blinding will be done whereby the examiners (2 dental surgeons) will not be aware of group allocation. Blinding of the participants and investigator will not be feasible as the principal investigator will train the peers to give oral health education and be engaged in distribution of oral health materials and treatment. The participants in intervention group will also receive peer delivered oral health education and treatments therefore they will know their group.

#### **4.10. Study outcomes**

The expected primary outcomes are improved oral health (dental caries status and gingivitis) and OHRQoL. The secondary outcomes include improved oral hygiene (plaque score) and oral health knowledge and related behaviors. The effect sizes for improvement in oral health and oral health related quality of life are based on average improvement achieved in similar studies reviewed.

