### **Gingivitis**

Is a site-specific inflammatory condition initiated by dental biofilm accumulation and characterized by gingival redness and edema and the absence of periodontal attachment loss (Trombelli *et al.*, 2018).

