## **2.0. Objectives**

### **2.1. Broad Objective**

To evaluate the effectiveness of applying the modified WHO basic package of oral care (BPOC) in improving oral health knowledge and related behaviors, oral health and OHRQoL among adolescents in Copperbelt, Zambia

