### **2.2. Specific Objectives**

- 1 To determine prevalence and distribution of dental caries, periodontal conditions and oral impacts on daily performance among adolescents in Copperbelt Province, Zambia
- 2 To determine the association between dental caries and oral health related quality of life among adolescents in Copperbelt Province
- 3 To assess the effects of a six months modified basic package of oral care intervention on knowledge and behaviors related to dental caries after 18 and 24 months of follow up.
- 4 To assess the effects of a six months modified basic package of oral care intervention on prevalence of dental caries after 18 and 24 months of follow up
- 5 To assess the effects of a six months modified basic package of oral care intervention on prevalence of oral impacts on daily performance after 18 and 24 months of follow up

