#### **4.9.2.4. Gingival bleeding**

Will be evaluated as bleeding on gingival on the index teeth (16, 11, 26, 36, 41, 46) and scored according to Silness-Löe index as follows:

- 0 = No inflammation (Normal gingiva, no discoloration, no bleeding)
- 1 = Mild inflammation (slight color change, mild alteration of gingival surface, no bleeding)
- 2 = Moderate inflammation (erythema, swelling, bleeding when pressure is applied)
- 3 = Severe inflammation (severe erythema and swelling and tendency towards spontaneous bleeding)

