#### **4.12. Data entry cleaning and analysis**

Data entry, coding and processing will be done using a computer software program IBM SPSS for Windows (Version 23). Frequency distribution for proportions, means (SD), cross tabulation with chi –square and binary logistic regression reported in odds ratio and 95% (CI) will be performed per respective objectives.

Frequency distribution for proportions of adolescents with plaque, gingival bleeding, poor oral health behaviors and oral health related quality of life. Dental caries experience will be summarized as number and percentage. Furthermore, cross tabulation for bivariate comparison of differences in intervention outcome variables by socio-demographics, study arms and oral health behaviors will be conducted. To examine for the differences between the groups (effectiveness of trial intervention) generalized estimating equations will be performed and reported in odds ratio and 95% confidence interval. A statistical significance difference shall be assumed when  $p \leq 0.05$ . Analysis plan per objective is summarized in appendix 6.

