#### **4.14. Study limitation and mitigation**

##### **Study limitations**

1. The follow up duration will be limited to 24 months which is enough to observe change in oral health related behaviors, plaque and bleeding but not reasonably enough for observing dental caries increment.
2. The study will follow single blind design where only the examiners will be blinded, the principal investigator and the participants will not be blinded due to the nature of the intervention which requires administration of educational technical materials and provision of treatment which cannot be easily concealed.
3. Adolescents may modify their oral health related behavior in response to awareness that there are being observed (Hawthorne effects).

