## Appendix 6- Analysis Plan by objectives

| No | Objective                                                                                                                                                                       | Analysis                                                                   | To be reported as                                              |
|----|---------------------------------------------------------------------------------------------------------------------------------------------------------------------------------|----------------------------------------------------------------------------|----------------------------------------------------------------|
| 1  | To determine prevalence and distribution of dental caries, periodontal conditions and oral impacts on daily performance among adolescents in Copperbelt Province, Zambia        | Frequency distribution, chi-square test, logistic regression               | Number and percentage, odds ratio with 95% confidence interval |
| 2  | To determine the association between dental caries and oral health related quality of life among adolescents in Copperbelt Province                                             | Frequency distribution, chi-square test, hierarchical logistic regression  | Number and percentage, odds ratio with 95% confidence interval |
| 3  | To assess the effects of a six months modified basic package of oral care intervention on knowledge and behaviors related to dental caries after 18 and 24 months of follow up. | Frequency distribution, chi-square test, generalized estimating estimation | Number and percentage, odds ratio with 95% confidence interval |
| 4  | To assess the effects of a six months modified basic package of oral care intervention on prevalence of dental caries after 6 and 12 months of follow up                        | Frequency distribution, chi-square test, generalized estimating estimation | Number and percentage, odds ratio with 95% confidence interval |
| 5  | To assess the effects of a six months modified basic package of oral care intervention on prevalence of oral impacts on daily performance after 18 and 24 months of follow up   | Frequency distribution, chi-square test, generalized estimating estimation | Number and percentage, odds ratio with 95% confidence interval |

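### Gingivitis is a primary outcome in section 4.10, but the specific effect objectives and the effect rows of Appendix 6 omit it, and elsewhere it becomes gingival bleeding

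*Protocol*

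**What the plan says.** Section 4.10 ranks the outcomes. For the primary ones it says: "The expected primary outcomes are improved oral health (dental caries status and gingivitis) and OHRQoL". Plaque score, and knowledge and behaviours, are secondary.

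The broad objective (2.1) is to evaluate effectiveness "in improving oral health knowledge and related behaviors, oral health and OHRQoL among adolescents in Copperbelt, Zambia". It does not name the gums. Among the specific objectives (2.2), only the first touches them, and it is descriptive: "To determine prevalence and distribution of dental caries, periodontal conditions and oral impacts on daily performance among adolescents". The effect objectives are 3 to 5. They cover knowledge and behaviours, caries, and oral impacts on daily performance. Section 4.12 refers to Appendix 6 for the analysis by objective, and that table repeats the same five topics. Row 3, for example, concerns the effect of the "intervention on knowledge and behaviors related to dental caries after 18 and 24 months of follow up".

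Elsewhere the gums are treated as an analysed outcome. The Summary includes gingival bleeding among the outcomes compared between groups. Section 4.11.2 lists it as a dependent variable. Section 4.12 plans a "Frequency distribution for proportions of adolescents with plaque, gingival bleeding, poor oral health behaviors" and then GEE with odds ratios for the effect of the intervention.

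On measurement, the definition of key terms describes gingivitis as an inflammatory condition "characterized by gingival redness and edema and the absence of periodontal attachment loss". Section 4.9.2.4, headed gingival bleeding, scores the index teeth from 0 to 3, and its second level reads "1 = Mild inflammation (slight color change, mild alteration of gingival surface, no bleeding".

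The first limitation in 4.14 calls 24 months of follow-up "enough to observe change in oral health related behaviors, plaque and bleeding". The same sentence says the period is not reasonably long enough for caries increment.

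**The concern.** Appendix 6 is the protocol's own analysis plan by objective. An analyst who follows it row by row makes a between-arm comparison for two primary outcomes and for one group of secondary outcomes, and makes none for the third primary outcome. An analyst who follows the Summary and 4.12 does compare the arms on it. Both have followed the protocol.

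Two choices are then open for a primary outcome: which visit or visits carry the claim, and what counts as a case. If these are settled after the data are seen, a reader of the trial report cannot tell a planned result from a selected one. It matters more here because, by 4.14, bleeding is a clinical primary measure that the protocol expects to be able to change within the follow-up, while it has doubts about caries increment.

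**Working it through.** The check is mainly a matching of text.

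**Step 1. Match each outcome in 4.10 to an effect objective (2.2) and a GEE row (Appendix 6).**

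| Outcome in 4.10 | Rank | Effect objective | GEE row | Months given |
|---|---|---|---|---|
| Dental caries status | primary | 4 | 4 | 18 and 24 in 2.2; 6 and 12 in Appendix 6 |
| Gingivitis | primary | none | none | none |
| OHRQoL | primary | 5 | 5 | 18 and 24 |
| Plaque score | secondary | none | none | none |
| Knowledge and behaviours | secondary | 3 | 3 | 18 and 24 |

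Two of the three primary outcomes are matched and one is not. Appendix 6 row 1, the only row that mentions periodontal conditions, lists frequencies, a chi-square test and logistic regression. It has no GEE and no intervention effect.

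**Step 2. Look for an effect analysis elsewhere.** The Summary, 4.11.2 and 4.12 together do provide one, under the name gingival bleeding. The broad objective also covers oral health, which 4.10 reads as caries and gingivitis. So this is a contradiction between parts of the protocol, not a complete absence.

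**Step 3. Look for an assessment time.** Section 4.9.1 sets follow-ups at 6, 12, 18 and 24 months and says that each variable is analysed at each of them. None is marked as primary for the gum outcome, and there is no objective from which a time could be taken.

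**Step 4. Compare the name with the codes.**
- Section 4.10 says gingivitis; 4.9.2.4, 4.11.2 and 4.12 say gingival bleeding.
- Code 1 is labelled mild inflammation, and gingivitis is defined as an inflammatory condition. On that reading, code 1 is a case of gingivitis but not of bleeding.
- Erythema and swelling, the signs in the definition, are first named at code 2, where bleeding on pressure also starts. On that reading, gingivitis and bleeding are the same set, codes 2 and 3.
- No cut-off is written. The text allows both readings.

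**Step 5. See whether the sample size settles anything.** Section 4.4 gives 4 × (1.96 + 1.03)² × 1.34² / 0.268² = 894.01. Multiplying by the design effect, 894 × [1 + (80 − 1) × 0.01] = 894 × 1.79 = 1600.26. Adding 10% gives 1600 × 1.10 = 1760. The stated figures are reproduced, but every outcome input is mean DMFT. No gum measure, case definition or time enters.

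**The case against.** The strongest reply is that the analysis is planned and only a table row is missing. The broad objective and the third research question cover the effect on oral health, the Summary names gingival bleeding in the between-group models, and 4.12 applies GEE to the intervention effect. Leaving the outcome out of the report would depart from the Summary. This stands as far as it goes: a reader of Appendix 6 might infer that the gums have no effect analysis at all, and the documents do not support that. It does not remove the contradiction with the table to which 4.12 itself refers.

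A second reply is that 4.9.1 has every variable analysed at every visit. That is so, but it gives four analyses and does not say which of them is primary.

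A third reply concerns code 1. A reader might infer that the protocol counts as healthy some pupils who have gingivitis by its own definition. The documents do not support this: no cut-off is written, and the defining signs are first named at code 2. A threshold for a recorded index is also commonly left to the statistical analysis plan, so its absence is not a fault in itself. What remains is that the primary outcome carries two names that may not mean the same thing.

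A fourth reply is that 4.14 does not say caries cannot respond, and that staging by CAST is offered as mitigation. That is correct, and the point does not depend on a stronger statement.

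**Conclusion.** The point holds as an internal contradiction. One of three declared primary outcomes has no specific effect objective, no effect row in Appendix 6 and no primary assessment time, while other sections treat it as an analysed outcome under a different name. Whether code 1 is a case is ambiguous, not stated.

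The size is in the scope of the confirmatory claim. A reader might go further and infer that the two case definitions would lead to different conclusions. That would need the distribution of codes in each arm and the movement between them, and the protocol gives neither; if gingivitis is taken to start at code 2, the two definitions coincide. The conclusion assumes only that Appendix 6 is meant to be the analysis plan by objective, as 4.12 says.

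**What to change.** - In 4.10, name the primary outcome as gingival bleeding, defined as at least one of the 12 index surfaces (six teeth, buccal and lingual) scored 2 or 3. Give code 1 or higher as a supportive analysis.
- In 2.2 and Appendix 6, add an effect objective and a GEE row for gingival bleeding at 18 and 24 months, the times that 2.2 gives for the other effect objectives.
- Reconcile Appendix 6 row 4, which gives 6 and 12 months, with Objective 4 in 2.2, which gives 18 and 24, so that the rows agree.
- Do not borrow a summed score as the supportive measure: the maximum of 36 in Appendix 2 is defined for the plaque index only.

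The cost is protocol wording and one table row. The surfaces are already scored on the clinical form, so no further data collection is needed. The drawback is that the trial's claim is limited to gingival bleeding and no longer covers the broader term gingivitis.

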#### **4.11. Study Variables**

##### **4.11.1. Independent variables**

Independent variables will include demographic variables of the adolescents (age and sex) and socio-demographics of the parent/guardian (father's education, mother's education, family size, number of children, and family material possession).

Socio-demographics of the parents or guardians will be assessed by four items;

1. Education of adolescent's father and mother will be assessed as the highest level of education attained and coded as {1=No formal education, 2=Primary education, 3=Secondary education, 4= College/University, 5=I don't know, 6= Not applicable}
2. Family size will be recorded as absolute total number of people in the participant's house including parents, children and other dependants constantly living with them (not including visitors) {1 up to the highest}
3. Number of children in the family will be recorded as absolute total number of children respectively in the participant's family {1 up to the highest}
4. Material possession will be assessed using international wealth index (Smits et al., 2015).

#### **4.11.2. Dependent variables**

The dependent variables to be evaluated will include oral health related behaviors (frequency of tooth brushing, use of fluoride tooth paste, frequency of sugar consumption, dental visits), oral health outcomes (plaque, gingival bleeding, dental caries status) and OHRQoL.

##### **4.9.2.1. Oral health related behaviors**

Adolescents will be requested to report their oral health related behaviors. In respect to tooth brushing, use of fluoridated tooth paste and sugar consumption they will be required to reflect their conduct in the past 30 days. Frequency of tooth brushing per day and use of fluoridated toothpaste will be assessed and recoded using a 4-point scale follows {1= I didn't, 2= I did but not every day, 3=I did once a day, 4 = I did twice a day or more}. Intake of sugar containing drinks or foods will be assessed and recorded using a 5-point scale as follows {1= I didn't take, 2= occasionally per week, 3= Once per day, 4= Twice to four times per day, 5 = Five times or more per day}. Visiting a dentist in past one year for checkup will be assessed and recorded based on a 3-point scale {1= I didn't attend, 2= I attended once, 3=I attended twice or more}

##### **4.9.2.2. Oral health related Quality of Life**

Oral Health Related Quality of Life (OHRQoL) will be assessed using Child –OIDP tool where the participants will be asked to rate how often in the past 30 days they had impact on their daily performance (eating or enjoying food, speaking or pronouncing words, cleaning teeth, sleeping and relaxing, smiling, laughing, showing teeth without embarrassment, enjoying contact with people, maintaining usual emotional state without being irritable, carrying out school activities such as attending class or social role) due to oral diseases and scored as follows: {1=Never, 2= Once or twice a month, 3= Once or twice a week, 4= Every or nearly every day}.

#### **4.9.2.3. Dental plaque**

Will be evaluated as a sticky colorless or pale yellow to brown biofilm on tooth surface (buccal and lingual) of the index teeth (16, 11, 26, 36, 41, 46) and scored based on to Silness-Löe plaque index as follows:

- 0 = Plaque not visible nor cannot be wiped off with the explorer
- 1 = Plaque not visible but can be wiped off with the explorer
- 2 = Plaque is visible along the gingival no need to probe
- 3 = Thick plaque is visible along gingival margin

#### **4.9.2.4. Gingival bleeding**

Will be evaluated as bleeding on gingival on the index teeth (16, 11, 26, 36, 41, 46) and scored according to Silness-Löe index as follows:

- 0 = No inflammation (Normal gingiva, no discoloration, no bleeding)
- 1 = Mild inflammation (slight color change, mild alteration of gingival surface, no bleeding)
- 2 = Moderate inflammation (erythema, swelling, bleeding when pressure is applied)
- 3 = Severe inflammation (severe erythema and swelling and tendency towards spontaneous bleeding)

#### 4.9.2.5. *Dental caries*

Will be evaluated as any visible change of enamel color or translucent to extensive distinct cavity with visible dentin or pulp cavity and coded according to Caries

Assessment Spectrum and Treatment (CAST) as follows:

| Characteristic      | Code | Description                                                                                                                                                        |
|---------------------|------|--------------------------------------------------------------------------------------------------------------------------------------------------------------------|
| Sound               | 0    | No visible evidence of a distinct carious lesion is present                                                                                                        |
| Sealant             | 1    | Pits and/ or fissure are at least partially covered with a sealant material                                                                                        |
| Restoration         | 2    | A cavity is restored with an (in)direct restorative material                                                                                                       |
| Enamel              | 3    | Distinct visual change in enamel only; a clear caries-related discoloration is visible, with or without localized enamel breakdown                                 |
| Dentine             | 4    | Internal caries-related discoloration in dentine; the discolored dentine is visible through the enamel, which may or may not exhibit a visible localized breakdown |
|                     | 5    | Distinct cavitation into dentine; the pulp chamber is intact                                                                                                       |
| Pulp                | 6    | Involvement of the pulp chamber; distinct cavitation reaching the pulp chamber, or only root fragments are present                                                 |
| Abscess/
fistula | 7    | A pus-containing swelling or a pus-releasing sinus tract related to a tooth with pulpal involvement                                                                |
| Lost                | 8    | The tooth has been removed because of dental caries                                                                                                                |
| Other               | 9    | Does not match with any of the other descriptions                                                                                                                  |

